## Abstract

**Background:**

First Nations children hospitalised with acute lower respiratory infections (ALRIs) are at increased risk of future bronchiectasis (up to 15–19%) within 24-months post-hospitalisation. An identified predictive factor is persistent wet cough a month after hospitalisation and this is likely related to protracted bacterial bronchitis which can progress to bronchiectasis, if untreated. Thus, screening for, and optimally managing, persistent wet cough one-month post-hospitalisation potentially prevents bronchiectasis in First Nations’ children. Our study aims to improve the post-hospitalisation medical follow-up for First Nations children hospitalised with ALRIs and thus lead to improved respiratory health. We hypothesize that implementation of a strategy, conducted in a culturally secure manner, that is informed by barriers and facilitators identified by both parents and health care providers, will improve medical follow-up and management of First Nations children hospitalized with ALRIs.

**Methods:**

Our trial is a multi-centre, pseudo-randomized stepped wedge design where the implementation of the strategy is tailored for each study site through a combined Participatory Action Research and implementation science approach informed by the Consolidated Framework of Implementation Research. Outcome measures will consist of three categories related to (i) health, (ii) economics and (iii) implementation. The primary outcome measure will be Cough-specific Quality of Life (PC-QoL). Outcomes will be measures at each study site/cluster in three different stages i.e., (i) nil-intervention control group, (ii) health information only control group and (iii) post-intervention group.

**Discussion:**

If our hypothesis is correct, our study findings will translate to improved health outcomes (cough related quality of life) in children who have persistent wet cough a month after hospitalization for an ALRI.

*Trial registration* ACTRN12622000224729, prospectively registered 8 February 2022, URL: https://www.anzctr.org.au/Trial/Registration/TrialReview.aspx?id=382886&isReview=true.

**Supplementary Information:**

The online version contains supplementary material available at 10.1186/s12890-022-01878-3.

## Background

Respiratory illnesses account for 12% of the age-standardised mortality gap between First Nations and other Australians [1]. Respiratory disease is the second most common cause for hospitalisation among First Nations people [2]. First Nations children hospitalised with acute lower respiratory infections (ALRIs) are particularly vulnerable to developing bronchiectasis [3, 4], with 15–19% of First Nations children having bronchiectasis within 24-months post-hospitalisation with pneumonia or bronchiolitis [3, 4]. Children who present with persistent wet cough a month after hospitalisation are specifically at risk because they likely have protracted bacterial bronchitis which can progress to bronchiectasis [5]. If children are screened for persistent wet cough one-month post-hospitalisation and managed optimally if wet cough is still present, then bronchiectasis can potentially be prevented. Culturally secure assessment [6] and treatment [7–9] is important for optimal outcomes in First Nations contexts. That is, ensuring First Nations Australians receive care that acknowledges their unique cultural needs and differences.

The study protocol follows the Standard Protocol Items: Recommendations for Intervention Trials [10] (SPIRIT) and reporting will follow the Standards for Reporting Implementation Research (STaRI) [11]. The Consolidated Criteria for Reporting Qualitative research [12] (COREQ) will be used to report qualitative data findings.

### Overall aim

To facilitate timely and effective post-hospitalisation follow-up of First Nations children hospitalised with ALRIs to optimise respiratory health.

### Specific objectives

To implement an effective medical follow-up strategy that will:Improve post-hospitalisation follow-up rates;Improve the quality of follow-up for First Nations children hospitalised with ALRIs;Improve the cough-related quality of life of First Nations children who have persistent wet cough one-month post-hospitalisation for ALRI;Determine the health-related economics of the strategy.Determine the best implementation practice for scaling up of the strategy.

## Methods

### Trial design

The study is a multi-centre, pseudo-randomized stepped wedge design where the medical follow-up strategy at each study site is implemented with consideration of barriers and facilitators using a combined Participatory Action Research (PAR) and implementation science approach, guided by the Consolidated Framework of Implementation Research. Outcome data for each site will be collected in three stages, as discussed below. The timing of interventions at individual study sites/cluster will not be randomised but determined by site-related logistics which will vary greatly (months to years) between sites (Fig. 1).

**Fig. 1 Fig1:**
[figure not shown]
Overview of trial design

### Participants, interventions and outcomes

#### Study setting

Settings include at least two Australian hospitals with an associated primary care health service that provides medical care to primarily First Nations.

Sites:Broome: Broome Hospital, Broome Regional Aboriginal Medical Service; Kimberley Aboriginal Medical Service Broome, Western AustraliaPort Hedland Health Campus, Wirraka Maya Aboriginal Medical Health Service Western Australia
We hope to extend the study to additional sites, pending funding. These additional sites are:3.Karratha Health Campus and Mawarnkarra Health Service4.Townsville hospital and local First Nations health service5.Cairns hospital and local First Nations health service

### Eligibility criteria

#### Participants

**Inclusion criteria:** Australian First Nations children aged 0–16 years hospitalised with ALRIs and their parents/carers (henceforth, respectfully called parents) who will serve as proxy for their children.

Three participant groups:**Nil-intervention control group**: Children hospitalised with ALRIs between 6-weeks to 6-months before commencement of our trial.**Health-information control group**: Prospectively recruited children hospitalised with ALRIs after commencement of the trial but before the implementation has commenced.**Post-intervention group**: Children hospitalised with ALRIs after the implementation of the strategy has commenced (from Day-1 of the implementation of strategy).

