### Health outcome/primary outcome measure (Quality of Life (PC-QoL))

The primary outcome is the parent-proxy Cough-specific Quality of Life (PC-QoL) for children with chronic wet cough. Effective follow-up and management of children hospitalized with ALRIs will be assessed by measuring PC-QoL between 6 weeks and 3 months after hospitalization. We will use the 8-item version of the PC-QOL tool that has been shown to be a valid, reliable, and responsive tool for measuring the burden of chronic cough in children. This tool has been used effectively in First Nations settings [17, 18].

Rationale: children with ongoing respiratory symptoms and cough post hospitalization will have improved quality of life if they receive effective medical follow-up at one-month post discharge. The PC-QoL scores will be compared pre and post implementation in different children who had a chronic wet cough post-discharge. Children with chronic wet cough post-hospitalization who received timely follow-up and optimal management will have better cough specific QoL than children who did not. It has been determined, using the anchor method, that 0.9 is the calculated minimum important difference in PC-QOL [23].

Respiratory symptoms after ALRI should typically resolve within 4 weeks. Children with ongoing wet cough 4 weeks post-hospitalization are likely to have protracted bacterial bronchitis that should resolve if detected and managed in a timely way. Hence, if children receive appropriate follow-up and management a month after discharge then we expect their cough related QoL to be better after 6–12 weeks than those who did not (waiting 6–12 weeks allows time for management to be completed in those children with chronic wet cough who may require up to a month of antibiotic treatment).

The PC-QoL tool will be administered by a research officer in-person at the hospital sites, over the phone, or electronically (online option via REDCap for those participants who would prefer this option). Participants will be contacted by the research officer via text message or telephone.

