### Secondary outcome measures

Cultural competency of HCP while child hospitalized (parent report).Instructions for medical follow up given by clinician (parent report).Follow-up rates of children within 1-month (range 3–6 weeks) post hospitalization for ALRI (parent report).In children with chronic wet cough:Antibiotics prescribed at follow-up (parent report).Adherence to prescribed antibiotics (self-report).Cough resolution at 6–12 weeks post discharge (parent report).Discharge summary audit: An audit of the discharge summary to evaluate patient management (see Additional file 6):First Nations ethnicity recorded.Local clinic/doctor identified.Instructions given to parent to follow up in 1-month with local doctor.Instructions to the local clinic/GP clearly stipulates to check child for ongoing chronic wet cough, absence or presence of ongoing other signs and suggest appropriate management if chronic wet cough is present. Link to appropriate clinical practice guidelines for the management of chronic wet cough provided.*Note: an audit of discharge summaries will be conducted each month. De-identified results (audit and feedback) will be provided to the HCPs each month at their regular departmental meeting to facilitate service improvement as part of implementation process.*
Secondary outcome measures 1–4 will be captured by telephone follow-up at 6–12 weeks post discharge. To ensure culturally secure engagement, a standardized script will be used to provide context by the telephoning research officer. The research officer who telephones the parent will first introduce themself and identify from where they are calling. The officer will provide context for the call, i.e., remind parent about the study and child’s recruitment at recent hospital admission. The questions are outlined in question 2, 3, 5 of Additional file 7.

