### Recruitment

#### Recruitment of Nil-intervention control group

A researcher will access hospital records of patients who have been previously (within the last 6-months) hospitalised at the hospital site with ALRIs. A recruitment letter will be sent to the parent from the hospital containing an overview of the study and opt-out instructions. If an opt-out response was not received within 3 weeks of posting the letter, a clinician researcher will contact the parent via telephone. The parent will be given the opportunity to consent via telephone. The questions will be administered via telephone.

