#### Recruitment of participants on hospital wards

**In General:**

Health-information control group and post-intervention group:Identified through hospital electronic record systems or equivalent to identify if a First Nations child has been admitted with an ALRI.A researcher will invite the parent, while on the ward ***during the child’s admission***, to participate in the study using the following process:Lung health information will be given to parents in a culturally secure way, which includes the use of an information flip chart [27].The study will be explained verbally and via written study information.Parents will be invited to participate in the study (with follow-up) and to consent or opt out of an interview.If consenting, an interview will be conducted.A First Nations researcher will be available for all interactions with First Nations participants.During recruitment, parents will be asked for the best contact number for a follow-up phone call to obtain follow-up data from parents.

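### The nil-intervention controls, as defined and contacted, do not fit the primary outcome window, so the primary contrast is confounded with time since discharge

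*Protocol article*

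**What the plan says.** Four parts of the protocol article fix when children are assessed.

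- **Outcome window** (Health outcome/primary outcome measure). Effective follow-up and management "will be assessed by measuring PC-QoL between 6 weeks and 3 months after hospitalization". The same section also words the window as 6–12 weeks: "we expect their cough related QoL to be better after 6–12 weeks than those who did not".
- **Control group** (Eligibility criteria, Participants). Nil-intervention controls are "Children hospitalised with ALRIs between 6-weeks to 6-months before commencement of our trial".
- **Control contact** (Recruitment of Nil-intervention control group). Records are searched for patients "previously (within the last 6-months) hospitalised at the hospital site with ALRIs", and a letter is sent. "If an opt-out response was not received within 3 weeks of posting the letter, a clinician researcher will contact the parent via telephone". "The questions will be administered via telephone".
- **Prospective groups** (Recruitment of participants on hospital wards; Secondary outcome measures). Parents are approached during the admission: "During recruitment, parents will be asked for the best contact number for a follow-up phone call to obtain follow-up data from parents". "Secondary outcome measures 1–4 will be captured by telephone follow-up at 6–12 weeks post discharge". The section on participant retention repeats the 6–12 week call.

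Under Statistical methods, the main result of the study is the nil-intervention versus post-intervention coefficient. The minimum model contains site, calendar week, sex and age. Time since discharge is not listed.

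**The concern.** A child admitted four to six months before commencement cannot be assessed at 6 weeks to 3 months by a call made after commencement. Children in the post-intervention group are enrolled on the ward, so their calls can be scheduled in the window. The two arms of the primary contrast would then be measured at different distances from the illness.

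The protocol itself treats that distance as important: it justifies the 6–12 week wait by the time needed for symptoms to resolve and management to finish. PC-QoL is scored only in children with chronic wet cough, expected to be about 20% of those recruited. Assessment time can therefore affect both the score and which children are scored. There is no randomisation to protect the contrast. Secondary outcomes 1–4, including cough resolution at 6–12 weeks, meet the same difficulty in the nil group.

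**Working it through.** **The plan's own figure.** With 12 per period, difference 1.6, SD 1.3 and two-sided alpha 0.05, power is 85.4% by the normal approximation and 82.1% by the noncentral t. This agrees with the stated figure of more than 80%. The power statement is not in error, but it presumes comparable assessment times.

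**Inputs.** Look-back 6 weeks to 6 months (6.0 to 26.1 weeks, a span of 20.1). Opt-out wait at least 3 weeks. Outcome window 6 weeks to 3 months (13.0 weeks), or 6–12 weeks in the other wording.

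**Assumptions.** Letters posted at commencement; admissions even over the look-back; stays short, so that counting from admission or from discharge makes little difference.

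**Formula.** Weeks since hospitalisation at the call = look-back + lag. Share in window = overlap with the window ÷ 20.1.

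| Lag | Weeks at call | In window, limit 3 months | In window, limit 12 weeks |
|---|---|---|---|
| 0 | 6.0–26.1 | (13.0 − 6.0)/20.1 = 35% | (12 − 6)/20.1 = 30% |
| 3 weeks | 9.0–29.1 | (13.0 − 9.0)/20.1 = 20% | (12 − 9)/20.1 = 15% |
| 6 weeks | 12.0–32.1 | (13.0 − 12.0)/20.1 = 5% | 0% |

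The share outside is therefore 80–85% with the 3-week wait and 65–70% with none. Later posting acts like a longer lag.

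**Mean gap.** Controls: (9.0 + 29.1)/2 = about 19.0 weeks. Post-intervention children at mid-window: (6 + 13.0)/2 = 9.5 weeks. The gap is about 9.5 weeks. With no lag it is 16.0 − 9.5 = 6.5 weeks.

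**Sensitivity to uneven admissions.** For half the controls to be inside the 3-month limit, the weekly admission rate in the qualifying most recent weeks would have to exceed the rate in the rest by a factor of (29.1 − 13.0)/(13.0 − 9.0) = 4.0. With no lag the factor is (26.1 − 13.0)/(13.0 − 6.0) = 1.9.

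**Restricting at analysis only.** Of the 20 controls aimed for (Pragmatic data collection), 20 × 0.20 = 4 would remain, or 20 × 0.35 = 7 with no lag. Against 20 post-intervention children, the noncentrality is 1.6/(1.3√(1/4 + 1/20)) = 2.25, giving power of about 57%. With 7 controls it is 1.6/(1.3√(1/7 + 1/20)) = 2.80, giving about 77%.

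**The case against.** The strongest reply is that the 9–29 week range is derived, not stated. The recruitment section does not say when letters are posted, whether they go in one batch or on a rolling basis, or from what date the six months are counted. Commencement is not defined, stage intervals vary by site, and the figure and timeline table are not visible here. Controls might be called from six weeks onward, before commencement. This stands as a limit on the percentages. It does not remove the mismatch: no visible section states rolling contact, and most controls remain outside even with no lag if calls start at commencement.

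The PC-QoL tool and the question script are also not shown, so it cannot be checked whether controls are asked about their present state or about an earlier period. Either way the groups differ. Under the first reading controls are measured later; under the second, a recollection over months is set against a contemporaneous report.

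The covariate list is a minimum, so weeks since discharge could be added. That helps in part. With the 3-week wait, the two groups share only about weeks 9 to 12 or 13, and outside that range the adjustment is extrapolation.

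Three stronger readings might be inferred, and the documents do not support them.

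- That children admitted in the last six weeks before commencement, who fall in no group, would have been in window. With the 3-week wait they would be called at 3–9 weeks, so with even admissions only about half would be.
- That the groups differ by as much as four months. The average gap is about 9.5 weeks; 29.1 − 12 = 17.1 weeks applies only to the extreme controls set against the latest post-intervention calls.
- That the bias favours the programme. Later assessment allows more natural resolution, which raises control scores, while selecting coughs that persist or are remembered lowers them.

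**Conclusion.** The concern holds in this form: the control definition and contact procedure, followed as written, do not fit the primary outcome window, and the primary contrast is confounded with time since discharge. Calendar week does not repair this, because it measures date and not elapsed time.

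Under posting at commencement and even admissions, 80–85% of controls are out of window, and 65–70% with no lag. Later posting worsens this. Only rolling contact before commencement, or admissions heavily concentrated in the most recent qualifying weeks, would bring most controls inside. The inconsistency between the sections is certain; the percentages are conditional. The direction and size of the bias on the PC-QoL scale cannot be derived from the documents. Because the defect lies in the main contrast and restriction at analysis loses most controls, it should be settled before control recruitment. Trial status says recruitment had not commenced.

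**What to change.** Reconcile the group definition, the control recruitment procedure and the outcome section, and state one upper limit for the window (12 weeks or 3 months).

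- Redefine the nil group so that its calls fall inside the window, using rolling contact before the health-information stage. Post letters only after the 3–6 week follow-up period has passed, for example at about 6–9 weeks with calls at about 9–12 weeks. An earlier letter describing the study could itself prompt the one-month visit and contaminate a group meant to have had no intervention.
- Record weeks from discharge to assessment for every child.
- Base the primary contrast on in-window assessments, with weeks since discharge as a covariate. Calls at 9–12 weeks centre on 10.5, against 9 for calls at 6–12 weeks, so a small difference remains to be adjusted for.
- Report any out-of-window controls separately, as a sensitivity analysis.

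The cost is an amendment through the ethics committees and a longer lead-in at each site, or fewer controls. As an illustration with even admissions, rolling posting that starts with the 3-week band already at 6–9 weeks needs 20.1 − 3 = about 17 weeks of posting to cover as many admissions as the present look-back, plus the 3-week wait. That is about 20 weeks, where a single mailing needs about 3. This is a real burden at sites with access problems. Restricting at analysis without changing recruitment is cheaper in the field but leaves only about 4 of 20 controls, or about 7 with no lag.

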#### Participant exclusion criteria

Non-First Nations children.Children over the age of 16 years.Children who have a diagnosis of cystic fibrosis.Children with a tracheostomy insitu or have been admitted to hospital to undergo this procedure.

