### Economic analysis

A stepped health economic evaluation will be undertaken to determine the cost-effectiveness of implementation and the economic cost-saving of cases with prevented bronchiectasis. Costs determined are: (i) Cost of provision of new service, including staffing, consumables, cost of training, electronic discharge system modifications; (ii) the extra cost of caring for a child with bronchiectasis over their lifetime for ~ 19% of children hospitalised with ALRI.

The economic evaluation aims to determine the cost of the implementation process, i.e., the cost of the medical follow-up strategy at a hospital and primary care clinic and to determine the cost-effectiveness of the program though evaluating the cost-saving from preventing bronchiectasis in children i.e., where a child who had chronic wet cough and received appropriate follow-up and management thereby resulting in resolution of the cough will be seen as a case of bronchiectasis prevented. Cost data for the economic evaluation will include all costs associated with implementation at the hospital and primary care clinic (i.e., the strategy cost) and will include costs such as training workshops, health organization changes in process or functions at both hospital and local primary care clinic, facilitation of staff behaviour change, including identification of champions, audit and feedback, identification of barriers and enablers, and ongoing engagement with facilitation of practice change. The cost of the implementation strategy will be based on the current implementation package at Perth Children’s Hospital (PCH), adapted for other participating hospitals. This is the best estimate based on data, thus far, to deliver this strategy at a hospital site.

The economic evaluation will present findings as a series of steps, first reporting the costs and outcomes of the strategy separately, then reporting a series of incremental cost-effectiveness ratios (ICERs) using a variety of key outcomes, including the number of children managed, and the estimated number of cases of bronchiectasis prevented.

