### Plans for assessment and collection of outcomes

A PC-QoL tool [23] will be administered to eligible participants (not attached here in for copyright reasons, but for tool provided). The PC-QoL tool [23] has eight questions rated on a Likert-scale, and administered using REDCap software. A researcher who is trained and skilled in REDCAP software will create, maintain and enter data onto the database for all sites.

Participants will have their unique medical record unit number attached to their data, so will be re-identifiable. The use of this unique identifier will also allow us to link multiple records for the same participant together, as it is anticipated that a small (but non-negligible) number of participants will have recurrent chronic wet cough and hence be likely to be captured on two or more occasions spanning different data collection periods. The database will be stored on a computer at a location requiring an access card swipe for access. The computer is accessed by a password lock. Participants’ information will only be used for the purposes of this research project and will only be disclosed with permission except where required by law.

It is anticipated that the results of this research project will be published and/or presented in a variety of fora. In any publication and/or presentation, information will be provided in such a way that a participant cannot be identified. Confidentiality will be maintained by removing all the identifiers and using the participant’s code number for data presentation.

The study team collecting data will be comprised of at least two individuals at each site, the First Nations research officer and clinician researcher. The clinician research lead, i.e., project coordinator, will monitor data collection and source documents during regular study meetings. Once a month, the project coordinator will verify the information that has been collected on the study database and monitor any missing data or errors in data entry. If regular errors in data entry or collection are noted, an action plan will be put in place.

All eligible participants will be included in the study. All researchers recruiting participants and collecting data will have a current Good Clinical Practice certification.

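### Known bronchiectasis is not an exclusion, yet the economic analysis would count a resolved cough in such a child as a case of bronchiectasis prevented

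*Protocol article*

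**What the plan says.** Eligibility is broad. The inclusion rule takes "Australian First Nations children aged 0–16 years hospitalised with ALRIs and their parents/carers", with no condition on earlier lung disease. Besides ethnicity and age, the exclusions are "Children who have a diagnosis of cystic fibrosis" and "Children with a tracheostomy insitu or have been admitted to hospital to undergo this procedure". The section on collection of outcomes adds "All eligible participants will be included in the study".

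The primary set is defined by symptom: "The primary outcome is the parent-proxy Cough-specific Quality of Life (PC-QoL) for children with chronic wet cough". The supporting rationale is that "Children with ongoing wet cough 4 weeks post-hospitalization are likely to have protracted bacterial bronchitis that should resolve if detected and managed" promptly. Prior bronchiectasis is neither a named model covariate (the list is a stated minimum) nor one of the example subgroups.

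The Economic analysis section then turns cough resolution into a disease outcome. A child with chronic wet cough who is followed up and managed, "resulting in resolution of the cough will be seen as a case of bronchiectasis prevented". This count feeds the cost-saving estimate and is one of the outcomes for which an incremental cost-effectiveness ratio (ICER) is planned.

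**The concern.** The eligibility rules and the counting rule do not fit together. A child already diagnosed with bronchiectasis can be admitted with an ALRI, enrol, still have a wet cough at four weeks, be followed up and have the cough settle. Under the rule as written, that child is credited as a prevented case of a disease present before the trial began. The error always runs the same way: it can only add to a stage's count. In the post-intervention stage this inflates the apparent benefit and lowers the cost per case prevented.

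There is a lesser point for the primary comparison. The stages are non-randomised calendar periods and are recruited differently: the nil-intervention group by letter and telephone from past records, the other two on the ward. The share of children with known bronchiectasis could therefore differ between stages, and no named covariate would pick that up.

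**Working it through.** **1. Following one child through the rules.** Take a First Nations child aged 0–16 with bronchiectasis diagnosed before the index ALRI admission.
- Inclusion criteria: met.
- Exclusion criteria: none applies.
- PC-QoL set: entered if chronic wet cough is present.
- Economic rule: if followed up, managed and resolved, counted as one prevented case.

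No step removes the child, and the last is false by definition. This needs no assumption about treatment effect.

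**2. Effect on the ICER.** Let ΔC be the incremental cost, E the incremental number of cases counted as prevented, and k the net number of those with a prior diagnosis.
- As written: ΔC/E. Corrected: ΔC/(E−k).
- Corrected over written: E/(E−k) = 1/(1−f), with f = k/E.

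The documents give neither E nor k. As a hypothetical, take E = 20, borrowing the target of 20 scored children per stage as an order of magnitude:
- k = 1 (f = 5%): 20/19 = 1.05
- k = 2 (f = 10%): 20/18 = 1.11
- k = 4 (f = 20%): 20/16 = 1.25

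With a smaller count each child weighs more: E = 10, k = 1 gives 10/9 = 1.11.

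**3. The plan's own power figures.** Inputs are from the Sample size section: SD 1.3, two-sided alpha 0.05, 4 clusters, COV 0.65, ICC 0.01. Power is from the noncentral t distribution, with design effect 1 + ((1 + COV²)m − 1) × ICC for m children per cluster per period.
- Single site, 12 per period, difference 1.6: noncentrality 1.6/(1.3 × √(2/12)) = 3.01; power 82.1% (stated: above 80%).
- Clustered, m = 5, difference 1.6: design effect 1.061; power 95.7% (stated: above 95%).
- Clustered, m = 10, difference 0.9: design effect 1.132; power 81.8% (stated: above 80%).

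All three reproduce, so the sample-size arithmetic is not in question.

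**4. Possible shift in the primary coefficient.** If the share with known bronchiectasis differs by Δp between the two compared stages, and their mean PC-QoL differs from the other children's by δ, the unadjusted difference moves by Δp × δ. Both inputs are hypothetical.
- Δp = 0.10, δ = 0.9: 0.09
- Δp = 0.20, δ = 0.9: 0.18
- Δp = 0.20, δ = 1.6: 0.32

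Against the stated minimum important difference of 0.9, these are 10%, 20% and 36%. That is enough to justify a sensitivity analysis, but is not evidence of bias.

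**The case against.** The strongest defence is that the population suits the trial. The strategy is a hospital-level service of training, discharge templates and reminders, delivered to all First Nations children with an ALRI. The third objective concerns cough-related quality of life in those with persistent wet cough at one month, whatever the cause. The rationale calls protracted bacterial bronchitis only likely, so it allows for other causes. All of this stands, and it is why these children belong in the PC-QoL set.

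A reader might go further and infer that they dilute the primary effect and cost power. Assuming no effect at all in 5% of the set, the 82.1% and 81.8% above fall to 78.1% and 77.8%. The documents do not support that inference. Nothing in them says such children gain less from follow-up. The planning means and SD come from the team's unpublished data, which may already include such children, so any dilution could be counted twice.

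A reader might also try to size the group. Assuming 2%, 5% or 10% of recruits have the diagnosis, and 80% of those still cough, then dividing by the plan's 20% with chronic wet cough gives 8%, 20% or 40% of the set. The assumptions drive that result entirely. The cited 15–19% is bronchiectasis found within 24 months after hospitalisation, not prevalence at entry, and cannot anchor it.

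Two further points carry some weight. The article refers to eligibility for PC-QoL assessment in a way that could imply criteria beyond wet cough, and the full protocol is not shown; but the article states no such criterion. The prevented-case rule is also an openly adopted convention, and ICERs will be reported on other outcomes, such as children managed. This limits the reach of the error but does not make the rule true for a child already diagnosed.

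**Conclusion.** The point holds for the economic count. As written, the eligibility and economic rules together credit a prevented case of bronchiectasis to any child with the diagnosis before the index admission whose cough resolves after follow-up. The direction within a stage is certain. The size is unknown, because the documents do not give the number of such children; the factors of 1.05 to 1.25 are illustrations only.

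The eligibility criteria are not shown to be wrong, nor is the primary analysis shown to be diluted or underpowered. For the primary coefficient, all that can be said is that the stages might differ in their share of these children, which a sensitivity analysis would address. This is a correction to a stated counting rule. It is best made before enrolment, and the article reports that recruitment had not commenced.

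**What to change.** - In all three stages, record for each consenting participant, from the hospital record, whether bronchiectasis was diagnosed before the index admission.
- Amend the Economic analysis section so that children with that diagnosis are not counted as prevented cases, either in the ICER or in the cost-saving estimate.
- Keep them in the PC-QoL set, the follow-up outcomes and the discharge audit, consistent with the third objective.
- Report the nil- versus post-intervention coefficient once more without them, as a sensitivity analysis, and tabulate their number by stage.

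The cost is one baseline field from records the study already uses and a slightly less favourable prevented-case count. No participant is lost from the primary analysis. Diagnoses absent from the hospital record, and bronchiectasis not yet diagnosed, would still be missed, and the report should say so. Excluding these children from the PC-QoL set is a debatable alternative that would shrink an already small set, and the documents do not require it.
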